### 2.8. Safety considerations

Participants may pause or stop the recording at any time, without providing a reason and without any negative consequence for their medical care. If fatigue, emotional distress, discomfort, or any other difficulty occurs during the interview, the recording may be interrupted or discontinued according to the participant’s preference and the investigator’s clinical judgement.

All assessments will be conducted by qualified clinical staff in a hospital-based psychiatric setting. If clinically relevant worsening, active suicidal ideation, suicidal behavior, severe anxiety, psychotic symptoms, or any other urgent clinical concern is detected, clinical care will take priority over study procedures and the situation will be managed according to usual clinical practice.

### 2.9. Ethical considerations and data protection

This protocol has been reviewed and approved by the local Research Ethics Committee, which complies with the established legal requirements for biomedical research, accredited by the Government of Navarra (University of Navarra Research Ethics Committee; reference code: 2026.110). The study will be conducted in accordance with the Declaration of Helsinki and with applicable National and European data protection regulations.

The VOICE-DEP study is observational and non-invasive, and does not modify clinical decision-making, treatment prescription, or usual psychiatric follow-up. The only study-specific procedure consists of audio recording a predefined section of the medical interview. It includes review of clinical variables collected in routine practice and administration of the clinical scales specified in the protocol. No pharmacological or interventional procedure is introduced by the study. All participants will receive verbal and written information about the study and will provide written informed consent before any study-related procedure. Participants will be informed that participation is voluntary and that they may withdraw at any time without any negative consequence for their subsequent medical care. The informed consent form will include authorization for access to clinical records when required for study objectives.

Participants will be identified using sequential study codes. Case report forms, reports and study communications will be identified using these codes. Only the sponsor, the investigator and authorized members of the research team, the Research Ethics Committee and competent health authorities, where applicable, will have access to identifiable study material.

Voice recordings and clinical data will be pseudonymized, stored securely and processed in accordance with applicable Spanish and European data protection regulations. Pseudonymized voice recordings will be transferred without distortion to secure NNBi servers. Recordings will be stored until 31 December 2029 and destroyed no later than 1 January 2030. NNBi servers are certified according to the Spanish National Security Framework at High level and ISO 27001. Technical and organizational safeguards will include encryption at rest and in transit, role-based access control, the principle of least privilege, robust authentication, environment segregation, access logging, backup encryption, recovery procedures and secure deletion at the end of the retention period.

Results will be reported in aggregate form. Individual-level voice recordings and transcriptions will not be publicly released because of privacy and re-identification risks.

### 2.10. Status and timeline of the study

This study was approved on 2026/05/08. The start date of the recruitment period for this study was 2026/05/21. Recruitment and data collection are ongoing and planned to continue until December 2027. Analysis and interpretation of the data are planned for February 2028. Final results report is planned for September 2028.

## 3. Discussion

The present manuscript describes a protocol for a longitudinal, hospital-based study aimed at developing and conducting an exploratory evaluation of speech-derived candidate digital biomarkers for the detection and monitoring of major depressive disorder. As a protocol paper, this discussion focuses on methodological considerations, anticipated challenges in study implementation, limitations inherent to the design, and plans for dissemination and protocol management, rather than on empirical findings.

### 3.1. Limitations and methodological considerations

Several limitations and anticipated challenges of the proposed protocol should be acknowledged, particularly those inherent to voice-based clinical studies that seek to balance standardization, ecological validity, and translational feasibility.

Although speech recordings are obtained under controlled hospital conditions, substantial inter-individual variability in speaking style, emotional expressiveness, and engagement during clinical interviews is expected. To balance standardization with clinical realism, a semi-structured, clinician-administered interview protocol is used to elicit naturalistic speech. This improves ecological validity and clinical relevance, but may introduce variability in speech content, duration, and topic coverage, which can in turn affect both acoustic and linguistic measurements.

Longitudinal data collection poses practical challenges. Repeated assessments increase participant burden and may lead to missed visits or incomplete follow-up data. To mitigate this risk, follow-up visits are scheduled within flexible time windows and all procedures are designed to be brief and minimally invasive. Nevertheless, some degree of attrition is anticipated and will be explicitly addressed in the analytical strategy.

The planned sample size remains moderate. While the longitudinal structure provides valuable information on intra-individual vocal trajectories, a moderate sample may limit statistical power, increase uncertainty in performance estimates, constrain the exploration of complex interaction effects, and raise the risk of overfitting, particularly for higher-dimensional or multimodal models.

Technical variability in recording conditions such as background noise or microphone positioning, may influence acoustic measurements. The protocol addresses this by using a standardized recording device and placement, while intentionally avoiding laboratory-grade equipment to maximize clinical applicability. This trade-off prioritizes real-world deployability over maximal signal fidelity and may reduce the signal-to-noise ratio for certain acoustic digital biomarkers.

The study is conducted in a single clinical center and focuses on Spanish-speaking participants, which may induce selection bias and restrict external validity across healthcare systems, dialects, or linguistic contexts. Dialectal variation across Spanish-speaking regions may influence acoustic, prosodic, and linguistic characteristics. Therefore, the findings will be interpreted within the linguistic and geographical context of the study population and will require future external validation in samples from other Spanish-speaking regions and sociolinguistic settings. However, this focus also addresses a relevant gap in the literature, which has been predominantly centered on English-language datasets.

Because of the observational design and treatment heterogeneity, changes in speech cannot be fully disentangled from the effects of specific treatments. Treatment-related analyses will therefore remain exploratory and will not support causal inference.

Residual variability related to the recording time of the day will be acknowledged as a study limitation.

Finally, clinician-administered scales are used as the primary reference standards, but they are themselves subject to measurement variability and do not constitute an objective ground truth. In addition, symptom-focused MADRS questions may influence some linguistic variables, particularly sentiment-related measures, which will therefore be interpreted cautiously. The present protocol does not aim to replace clinical judgment but rather to complement it by identifying speech-derived markers that correlate with established measures of depressive severity.

In summary, the formal clinical diagnosis will define the study groups, whereas the MADRS, CGI, and PHQ-9 will be used to quantify symptom severity and longitudinal change. Speech-derived measures will therefore be interpreted as complementary correlates of clinical assessment rather than as independent objective standards, under the premise of supporting, but not replacing, the clinical judgment.

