## 2. Materials and methods

### 2.1. Aim of the study, design and setting

The overall aim of the VOICE-DEP study is to develop and formalize a standardized, reproducible and clinically grounded protocol for the multimodal analysis of voice and speech during medical interviews as a tool to support the diagnosis and longitudinal monitoring of depressive disorder.

The working hypothesis is that major depressive disorder and its clinical evolution are associated with changes in acoustic, paralinguistic and linguistic characteristics of voice and speech, and that these changes can be analyzed in a standardized and reproducible manner in a routine clinical setting.

**Primary objective.** The primary objective is to establish a reproducible clinical framework for extracting and analyzing acoustic, paralinguistic and linguistic features from semi-structured medical interviews, allowing discrimination between patients with a medical diagnosis of depressive disorder and healthy controls using voice-based models anchored to validated clinician-rated clinical reference standards.

**Secondary objectives.** The secondary objectives are: i) To construct a longitudinal Spanish-language clinical speech corpus including repeated voice recordings from patients with depressive disorder and single-session recordings from healthy controls; ii) To characterize the association between speech-derived digital biomarkers and clinician-rated measures of depressive severity, including their evolution over time; iii) To evaluate the added value of multimodal models combining acoustic, paralinguistic and linguistic features compared with unimodal models; iv) To assess intra-individual vocal changes across repeated assessments and their association with changes in clinical severity; v) To provide a transparent methodological framework that may facilitate replication, cross-study comparison and future external validation in other clinical presentations, diagnoses, languages and sociocultural settings; vi) To explore whether specific treatment modalities are associated with greater changes in voice and speech in parallel with clinical evolution.

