### 2.3. Study procedures and visit schedule

Participants will be recruited consecutively according to eligibility criteria. Patients will be invited by physicians from the research team during routine clinical practice. Healthy controls will be invited by members of the research team and, if they agree to participate, will be referred to a physician from the research team for baseline assessment. As this is an observational study, no randomization or blinding procedures will be applied.

At the baseline visit (V0), all participants will receive verbal and written information about the study objectives, methodology, non-invasive nature of the procedures, confidentiality safeguards, and exclusive research use of the collected data. Written informed consent will be obtained before any study-related procedure. A clinical interview will then be conducted to collect baseline sociodemographic and clinical information, followed by psychometric assessment using the clinical instruments specified in the protocol. During the same session, voice recordings will be obtained under standardized conditions.

Only patients with depressive disorder will undergo longitudinal follow-up. Patients will attend four additional visits coinciding, whenever possible, with routine psychiatric follow-up visits: V1 at 30 days, V2 at 60 days, V3 at 90 days and V4 at 120 days, each with an allowed window of ±7 days. At each follow-up visit, the same recording and clinical assessment procedures applied at baseline will be repeated. Clinician-rated and self-reported measures of depressive severity will be updated, and relevant clinical changes, including treatment adjustments or adverse events, will be documented. Healthy controls will complete only the baseline visit under the same recording conditions.

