In all participants, data collection will be integrated into the clinical interview. Only the part of the medical interview corresponding to the MADRS assessment will be audio recorded. In order to combine open ended questions by clinicians that allow patients to describe their experiences in their own words, allowing spontaneous and elaborated responses, while adopting a reliable method of exploration, the instructions of Montgomery and Asberg for the MADRS will be adopted, moving from broadly phrased questions about each symptom to more detailed ones which allow a precise rating of severity [27]. The recorded material will comprise the complete MADRS-related clinical interaction, including an initial free-speech segment immediately followed by the semi-structured questions used to complete the scale. The free-speech segment will be an introductory part of the recorded MADRS assessment (namely, patients will be asked to describe, in their own words, how they have been feeling in the past week). This recorded segment is expected to last approximately 10–30 minutes including the initial free-speech segment, allowing voice and speech to be collected within a clinically meaningful interaction while maintaining a standardized procedure.

Voice recordings will be assigned a pseudonymized audio identifier linked to participant type, participant code and visit number. Any relevant recording incident, including interruption due to patient need, clinical need or technical problems, will be documented in the case report form and considered in data quality assessment.

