### 2.6. Variables

All study variables will be recorded in a pseudonymized case report form developed specifically for the VOICE-DEP study. Variables will be classified into: (i) baseline variables collected only at V0, and (ii) longitudinal visit variables collected at V0, V1, V2, V3 and V4 in patients with depressive disorder.

Exposure variable: The main exposure variable is the medical diagnosis of moderate or severe unipolar depressive disorder, with or without psychotic symptoms, according to the predefined ICD-10 categories included in the protocol.

Primary outcome variables: The primary outcome variables are the standardized voice recording and the multimodal speech- and speech-derived variables extracted from the recorded clinical interview. These variables will be grouped into acoustic, paralinguistic and linguistic domains.

Clinician-rated and self-reported symptom variables: At each study visit, depressive symptom severity and global clinical status will be assessed concurrently with the voice recording using the MADRS, the Clinical Global Impression scale (CGI), and the Patient Health Questionnaire-9 (PHQ-9). These variables will provide the clinical reference outcomes for cross-sectional and longitudinal analyses. Psychotic depression, operationally defined by an ICD-10 diagnosis of F32.3 or F33.3, will be recorded as a binary clinical variable. The same clinician-rated and self-reported assessments will also be conducted in healthy controls at baseline (V0) to identify possible subthreshold symptoms.

Baseline and longitudinal variables: Baseline variables collected at V0 will include demographic, anthropometric, clinical and contextual information, including psychiatric and medical history, substance use, stressful life events, and previous depressive episodes. Longitudinal variables collected across visits will include recording traceability variables, symptom scales, pharmacological treatment variables, psychotherapy variables and neurostimulation-related variables.

Metadata related to the recording process, including pseudonymized audio identifiers and recording incidents, will also be documented for traceability and quality control purposes.

The complete list of study variables operationalized in the VOICE-DEP case report form is summarized in Table 2. The list of multimodal voice- and speech-derived variables is summarized in Table 3.

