### 2.7. Statistical and analytical plan

The analytical strategy of the VOICE-DEP study is designed to support the primary and secondary objectives of the protocol while ensuring methodological transparency, reproducibility, and robustness. In accordance with the study design, the analysis will address three complementary dimensions: (i) descriptive characterization of the study sample and extracted variables, (ii) exploratory cross-sectional association and discrimination analyses between patients with depressive disorder and healthy controls, and (iii) longitudinal intra-individual modeling of changes in voice- and speech-derived variables in relation to clinical evolution.

First, a descriptive analysis will be performed for all study variables recorded in the case report form. Quantitative variables, including acoustic, paralinguistic, and linguistic features, will be summarized using means and standard deviations or medians and interquartile ranges, as appropriate according to their distribution. Qualitative variables will be described using absolute frequencies and percentages. This descriptive phase will include both baseline variables collected at V0 and longitudinal variables collected across repeated visits in patients. Age, sex, educational level and available socioeconomic-related variables will be compared between groups and considered as covariates in adjusted or sensitivity analyses when relevant imbalance is observed and the sample size permits stable estimation.

Second, the association between continuous voice- and speech-derived digital biomarkers and clinical severity measures will be explored using Pearson or Spearman correlation coefficients, depending on distributional assumptions. These analyses will focus on the relationship between multimodal voice-derived variables and clinician-rated depressive symptom severity measured with the MADRS, global clinical status measured with the CGI, and self-reported depressive symptom burden measured with the Patient Health Questionnaire-9 (PHQ-9).

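### For the severity objectives, the MADRS is scored from the same conversation that supplies the voice features, so rating error can be shared with the voice and inflate the association

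*Protocol article*

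**What the plan says.** **The recording (Section 2.3).** "Only the part of the medical interview corresponding to the MADRS assessment will be audio recorded". "The recorded material will comprise the complete MADRS-related clinical interaction", that is, the opening free speech followed by the questions from which the scale is completed.

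**The ratings.** Section 2.6 states that at each visit "depressive symptom severity and global clinical status will be assessed concurrently with the voice recording using the MADRS", together with the CGI and PHQ-9. Section 2.3 adds that "no randomization or blinding procedures will be applied". The article describes no second rater, no rating made without hearing the patient, and no speech sample separate from the rating interview.

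**The use.** Secondary objective ii (Section 2.1) is "To characterize the association between speech-derived digital biomarkers and clinician-rated measures of depressive severity, including their evolution over time". Objective iv relates vocal change within patients to change in clinical severity. Under Section 2.7, the association of features with MADRS, CGI and PHQ-9 "will be explored using Pearson or Spearman correlation coefficients, depending on distributional assumptions", and mixed-effects or change-score models relate their trajectories.

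**The stated limits (Section 3.1).** "clinician-administered scales are used as the primary reference standards, but they are themselves subject to measurement variability". The section also warns that symptom-focused questions may affect some linguistic variables, chiefly sentiment. It says that the diagnosis defines the groups and that speech measures will be read as complements to clinical assessment, not as independent standards.

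**The concern.** One conversation yields both variables in the association. If slow, flat or halting speech moves the clinician's score beyond what the patient's true severity warrants, the error in the rating is correlated with the acoustic and paralinguistic features. A feature can then correlate with the MADRS partly because the rater was listening to it.

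The two limitations already in Section 3.1 describe something else. Measurement variability, read as independent noise, pulls a correlation towards zero. The caution on sentiment is about questions shaping the patient's words, not about the voice shaping the score, and it singles out sentiment-type linguistic measures. Pitch, pauses and speech rate carry no such caution.

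At stake is how objectives ii and iv are read. Further recordings of the same kind cannot separate voice following illness from ratings following voice. False-discovery control deals with chance findings, not with a systematic component of the correlation.

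**Working it through.** **1. The plan's own figure.** Section 2.4 gives a detectable difference of about d = 0.70 for 25 against 50 at two-sided 0.05 and 80% power. Normal approximation: (1.960 + 0.842) × √(1/25 + 1/50) = 0.686; noncentral t gives 0.695. The figure reproduces. It concerns the patient/control comparison and is not in dispute.

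**2. Shared-error model.** Write the rating as M = √R·T + √(1−R)·E, where T is true severity, E is rating error and R is reliability. Let a feature correlate a with T and b with E. Then

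corr(feature, M) = a√R + b√(1−R).

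The second term is the built-in part. The documents give neither R nor b, so both are assumed: R = 0.7 to 0.9 and b = 0.2 to 0.4.

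- No true link (a = 0). Smallest: 0.2 × √0.1 = 0.06. Largest: 0.4 × √0.3 = 0.22.
- Rejection rate of a nominal 5% test of one feature (Fisher z, a = 0): 6% to 18% at n = 25 (patients at V0), and 8% to 47% at n = 75 (if patients and controls are pooled at V0; the article does not say whether they are).
- Modest true link (a = 0.3). With independent error (b = 0), r = 0.25 to 0.28. With shared error, r = 0.35 (R = 0.9, b = 0.2) to 0.47 (R = 0.7, b = 0.4).

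**3. A second parameterisation, within patients.** Let a share s of within-patient MADRS variance come from vocal impression, and let a feature correlate c with that impression and not with true severity. The induced correlation is r = c√s.

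| Assumed c | Assumed s | Induced r |
|---|---|---|
| 0.3 | 0.05 | 0.07 |
| 0.5 | 0.10 | 0.16 |
| 0.7 | 0.05 | 0.16 |
| 1.0 | 0.10 | 0.32 |

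The last two rows assume that one extracted feature nearly reproduces the rater's vocal impression, so they are the high end.

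**4. What the analysis would make of it.** Complete follow-up gives 25 × 5 = 125 patient recordings and 125 − 25 = 100 within-patient degrees of freedom, or about 98 after covariates. By Fisher z with √95, r = 0.16 and 0.32 (the high-end rows) are declared significant at an unadjusted 0.05 with probability 0.34 and 0.89.

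Section 2.7 applies Benjamini–Hochberg within feature family. Table 3 lists about 44 acoustic scalars: pitch 3, intensity 2, MFCCs 26, harmonic-to-noise ratio 1, jitter 1, shimmer 1, spectral 3, formants 6, entropy 1; embeddings are excluded. At the strictest step, 0.05/44, the same two probabilities fall to about 0.04 and 0.48. The procedure is less strict than this when many features are affected together. Attrition, which Section 3.1 expects, lowers all of these figures.

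**The case against.** The case for leaving the plan alone has real content.

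- **The claim is already bounded.** Section 3.1 denies that the scales are objective ground truth and treats speech measures as correlates of clinical assessment. Section 2.4 calls classifier results exploratory. This limits the harm. It does not tell a reader that the correlation may be partly produced by the rater listening, and exploratory status does not remove a directional bias.
- **PHQ-9 is already analysed** in both the correlations and the longitudinal models. This stands: what is missing is its designated role, not the analysis.
- **Scope.** A reader might infer that the primary discrimination analysis is contaminated. The documents do not support that, since the ICD-10 diagnosis is its label. Nor do they show that the CGI rests wholly on the recorded speech: it is rated in the same session, but only part of the interview is recorded.
- **Mechanism.** The article does not list MADRS items, so it does not establish that any item is scored on observed manner. If one is, the manner may belong to the construct, and removing the item would discard some valid signal.
- **Size.** An r of 0.32 and a 0.89 chance of significance are tempting headline figures, but they need c near 1, no multiplicity adjustment and complete follow-up.
- **A pass/fail rule** requiring PHQ-9 and MADRS associations of similar size would be unsound. It has no margin, 25 patients cannot demonstrate similarity, and self-report differs from clinician rating for other reasons.
- **The case report form is only summarised** in Table 2, so nothing shows that item scores are not stored.

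**Conclusion.** The concern holds for secondary objectives ii and iv. The shared source is explicit for the MADRS and partly inferred for the CGI. The limitations in Section 3.1 do not cover rating error that runs with the voice.

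The size of the bias cannot be derived from the documents. Under the assumed inputs above, the induced correlation is roughly 0.06 to 0.3, before Benjamini–Hochberg adjustment and attrition. It inflates the association only where the rating error runs in the same direction as the expected voice–severity relation. This calls for a modest change to analysis and reporting. It does not undermine the design, and it leaves the patient/control classification and the d = 0.70 sensitivity figure as they are.

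**What to change.** 1. **Section 2.7:** designate the planned PHQ-9 association as the rater-independent check, acknowledging that it is only partly independent because it comes from the same visit. For each feature, report it beside the MADRS estimate with confidence intervals and note whether the signs agree. Set no similar-size gate.
2. **Section 2.7:** consult the MADRS scoring instructions. If any item is rated on observed manner, repeat the MADRS analyses without it as a sensitivity analysis, keep the total score as the main analysis, and confirm that item scores are stored.
3. **Section 3.1:** state that ratings and features share a source, so that a MADRS or CGI association not supported by the PHQ-9 is not read as independent evidence that voice tracks severity.

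**Cost:** slightly more analysis, a somewhat weaker claim and, if item scores are not already kept, item-level entry. No visit or patient assessment is added. Recruitment runs to December 2027 and analysis is planned for February 2028, so there is time. PHQ-9 associations may be weaker, or may differ for reasons other than listener bias, and dropping an item may remove some true construct.
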